#### Five-year follow-up outcome measures

At follow-up, we will report on whether:Opportunistic screening for COPD by social nurses has an impact on the rate of hospital contacts. This is assessed by examining the number of hospital contacts per person year within each year of the 5-year follow-up (both outpatient visits and hospitalizations) with a diagnosis related to COPD for three patient groups: (1) the group with no previous COPD diagnosis, impaired lung function at screening, and who underwent further assessment, (2) the group of patients with previous diagnosed COPD and impaired lung function at screening, and (3) the group with no previous COPD diagnosis, impaired lung function at screening, and who declined further assessment (Fig. 1).Opportunistic screening for COPD by social nurses has an impact on the use of COPD medication. This is assessed by examining number of prescriptions filled for COPD medications for two patient groups: (1) the group with no previous COPD diagnosis, impaired lung function at screening, and who underwent further assessment, and (2) the group of patients with previous diagnosed COPD at (Fig. 1). The reporting of medication will be organized into distinct categories, encompassing bronchodilators, corticosteroids, rescue medications, and maintenance therapies. Within each of these groups, the dosage prescribed or dispensed will be quantified.

Previous or no previous COPD diagnosis is assessed by the questionnaire at the time of screening as a patient-reported outcome. The lung function impairment is defined as FEV1/FVC ratio < 0.7. In the reporting, patients are stratified into groups with confirmed and non-confirmed COPD diagnosis.

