**Fig. 1 Fig1:**
[figure not shown]
Flowchart indicating the three patient groups with COPD and the process of study-inclusion and 5-year follow-up: (1) undiagnosed COPD at inclusion who underwent further assessment, (2) previously diagnosed with COPD at inclusion, (3) COPD at inclusion who declined further assessment

The app AIR MD algorithm selects the best of three forced expiratory manoeuvres. The app algorithm also informs the nurse about the precision grade and if the result is acceptable.

Participants with identified impaired lung function, that is a FEV1/FVC ratio below 0.7 or the values of FEV1 and/or FVC below 80% of the predicted value, will be referred to the respiratory outpatient clinic at the hospital for further diagnostic work-up. This referral protocol is applicable irrespective of whether the participant has a pre-existing lung condition or not. In cases where it is not feasible for patients to be seen at the respiratory outpatient clinic, they are instructed to contact their general practitioner for subsequent evaluation and management.

Finally, the social nurse asks the patient about their motivation to quit smoking. In addition, they receive information about available options for smoking cessation support, including hospital resources or referrals to cost-free municipal smoking cessation services.

Coordination regarding follow-up assessment, follow-up care, and general support from social nurses constitutes standard care and is not a part of the intervention but should be taken into account in interpreting the findings.

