#### Clinical variables

The patients enrolled in this study may be categorized into four groups according to their diagnostic status: those previously diagnosed with COPD (self-reported), those identified as having COPD through screening, those without COPD as determined by screening, and those with an unknown diagnostic status due to insufficient lung function test. COPD identified through screening refers to people whose post-bronchodilator FEV1/FVC ratio is less than 0,7, according to the measurements obtained by the social nurse.

When assessing the prevalence of COPD, the groups diagnosed through screening and self-reported COPD are considered. Participants who are unable to perform spirometry are classified as having an unknown diagnostic status and are not included in the calculation of COPD prevalence.

At the 5-year follow-up, the prevalence of patients diagnosed with COPD after screening is identified either through the National Patient Health registry based on the ICD10 code J.44 or by examining prescriptions for COPD medication (including all types of inhalation medicine) recorded in The Danish National Prescription Database.

The utilization of healthcare services is evaluated based on all hospital contacts, including outpatient visits, admissions, and emergency department (ED) visits.

Admission diagnosis and department will be included as descriptive variables - partly to ascertain whether there are patterns in where the screening has the greatest impact, and partly to assess whether there is selection bias in the study.

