### Statistical considerations

Continuous variables will be presented as mean with standard deviation if the variable can be assumed to be normally distributed, otherwise, the median and interquartile range will be presented. Categorical variables will be presented with frequencies for each level and their corresponding percentages.

The prevalence of COPD in the study population will be compared to the prevalence in the Danish general population using an unadjusted test of the ratio of proportions, with a normal approximation of the logarithm of the ratio.

Since participants can die or otherwise drop out during the follow-up period, participants contribute with different follow-up lengths. The number of contacts in the follow-up period will therefore be reported as a rate (contact rate) of the number of contacts divided by the follow-up length, that is as contacts per year.

The healthcare contact rate will be compared among the three previously described COPD groups: undiagnosed COPD at inclusion who underwent further assessment, undiagnosed COPD without further assessment, and previously diagnosed COPD at inclusion, using a Poisson regression model. The model will include potential confounders as independent variables in addition to the COPD groups.

Sub-analyses for the rate of acute contacts and outpatient contacts will be conducted using models constructed in the same way as for all contacts.

Medication usage as a rate: number of prescriptions per year. Likewise, a Poisson regression model will be used to compare the rates among the COPD groups. However, the groups will be divided into no COPD versus diagnosed COPD. We will employ rigorous control for potential confounders. Specifically, age, smoking history, and comorbidities will be included as covariates in our models.

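### The impact statement on hospital contacts rests on a total that includes the clinic visits the referral creates, so it can be null or above 1 even if acute contacts fall

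*Protocol article*

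**What the plan says.** Under Five-year follow-up outcome measures, the Protocol article sets out to report whether "Opportunistic screening for COPD by social nurses has an impact on the rate of hospital contacts". The measure follows directly: "This is assessed by examining the number of hospital contacts per person year within each year of the 5-year follow-up (both outpatient visits and hospitalizations", limited to contacts with a COPD-related diagnosis. No direction of benefit is attached to it.

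Three groups are compared. Group 1 is "the group with no previous COPD diagnosis, impaired lung function at screening, and who underwent further assessment", group 2 has a previous diagnosis, and group 3 is "the group with no previous COPD diagnosis, impaired lung function at screening, and who declined further assessment".

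Clinical variables also pools the contact types: "The utilization of healthcare services is evaluated based on all hospital contacts, including outpatient visits, admissions, and emergency department (ED) visits".

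Under Statistical considerations, "The healthcare contact rate will be compared among the three previously described COPD groups" by Poisson regression on all contacts. The split appears one paragraph later: "Sub-analyses for the rate of acute contacts and outpatient contacts" are to use models built in the same way.

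Under Methods, in the text after the Figure 1 caption, participants with impaired lung function "will be referred to the respiratory outpatient clinic at the hospital for further diagnostic work-up". Where that is not feasible, they are told to contact their general practitioner.

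**The concern.** The total adds two kinds of contact that need not mean the same thing. A clinic visit after a positive screen is the intended result of the referral. An acute admission or emergency visit for COPD suggests deterioration. One count treats them alike, so a higher rate may mean better access or worse disease, and opposite movements can cancel.

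There is also a problem of construction. Group 1 is defined by having been assessed and group 3 by having declined. Where the assessment took place at the hospital clinic and was coded to COPD, it is a contact of the kind being counted. Follow-up runs from the date of inclusion, so the visit falls inside it, and nothing in the article removes it. The group 1 versus group 3 ratio is then pushed upward before any effect of care.

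At stake is the reading of the contact outcome under the article's second objective, the five-year impact of screening and referral.

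**Working it through.** **Plan's own figures.** The article gives no contact rate, outpatient share or expected rate ratio. Its one computed figure, 511 patients, concerns the prevalence comparison and has no bearing here. All rates below are assumptions, used to show a range.

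**Step 1: how the total behaves.** Let s be the outpatient share of contacts in the comparison group, and RR_out and RR_hosp the two component rate ratios. Then

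RR_total = s × RR_out + (1 − s) × RR_hosp.

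Setting RR_total = 1 gives the outpatient ratio that exactly hides a fall in hospitalizations:

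RR_out = [1 − (1 − s) × RR_hosp] / s.

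| s (assumed) | RR_hosp = 0.70 | RR_hosp = 0.80 |
|---|---|---|
| 0.3 | (1 − 0.49)/0.3 = 1.70 | (1 − 0.56)/0.3 = 1.47 |
| 0.5 | (1 − 0.35)/0.5 = 1.30 | (1 − 0.40)/0.5 = 1.20 |
| 0.7 | (1 − 0.21)/0.7 = 1.13 | (1 − 0.24)/0.7 = 1.09 |
| 0.8 | (1 − 0.14)/0.8 = 1.08 | (1 − 0.16)/0.8 = 1.05 |

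The larger the outpatient share, the smaller the outpatient rise needed. The total can also go above 1: with s = 0.7, RR_out = 1.3 and RR_hosp = 0.7, it is 0.7 × 1.3 + 0.3 × 0.7 = 0.91 + 0.21 = 1.12. Modelled separately, the same data would show 1.3 and 0.7.

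**Step 2: the group-defining visit.** One counted visit per patient adds 1/5 = 0.2 contacts per year over five complete years, and up to 1.0 to the year-1 rate. Let r be the rate in group 3, and suppose group 1 is otherwise identical and every member has one such visit. The ratio is then (r + 0.2)/r over five years and (r + 1)/r in year 1.

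| r per year (assumed) | Five-year ratio | Year-1 ratio |
|---|---|---|
| 0.4 | 0.6/0.4 = 1.50 | 1.4/0.4 = 3.50 |
| 1.0 | 1.2/1.0 = 1.20 | 2.0/1.0 = 2.00 |

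These are upper values. A patient assessed by a general practitioner adds no hospital contact, and a clinic visit without a COPD-related code would not count under the outcome definition. If only a fraction q of group 1 has a counted visit, the additions become 0.2q and q.

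**Step 3: do the sub-analyses repair the total?** They would reveal opposite movements, because each rate gets its own model. They may not split the total exactly. The outcome section names outpatient visits and hospitalizations, whereas the sub-analyses name acute and outpatient contacts. Acute contacts may include emergency visits and leave out planned admissions.

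**The case against.** The strongest reply is that both components are already planned with the same model, so a reader of the results would see them beside the total. That stands, and it confines the point to the total. A reader might infer that the plan could miss a benefit altogether, or that the contact analysis as a whole cannot be interpreted. The planned sub-analyses contradict that.

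A reader might also infer that treatment is meant to lower hospitalizations. The article does not say so. The Abstract's anticipated results name survival, and the Introduction speaks of reducing disease progression and morbidity. A fall in acute contacts is a reasonable expectation, but it is not a stated aim.

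The total is nowhere labelled primary and no power attaches to it. This is true, yet the outcome section ties the impact wording to the pooled rate alone, and the split appears only as a sub-analysis. A total does answer a neutral question about utilisation. It does not distinguish access from deterioration.

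Reporting by year of follow-up helps to isolate visits made soon after referral, but it does not separate contact types within a year. Referral also applies to patients with a known lung condition, so group 2 is referred as well. That weakens the argument for group 1 versus group 2, but not for group 1 versus group 3.

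Finally, the acute rate is itself open to self-selection, since patients who accept assessment may differ from those who decline. That stands, and the change proposed here does not cure it.

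**Conclusion.** The point holds for the total on which the impact statement rests. As written, that ratio includes contacts generated by the referral and, for patients seen at the hospital clinic with a COPD-related code, the visit that defines group 1. It can be null or above 1 while acute contacts fall.

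The size cannot be taken from the article. The masking range for a 30% fall in hospitalizations (an outpatient ratio of 1.08 to 1.70) rests on assumed outpatient shares of 0.8 to 0.3. It shows that cancellation is possible, not that it is likely. The push from the group-defining visit further depends on how many of group 1 were assessed at the hospital rather than by a general practitioner.

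**What to change.** - Let the rate of acute contacts, defined as acute admissions and emergency department visits, carry the impact statement on hospital contacts.
- Report outpatient visits beside it as a measure of care uptake, and state in advance the expected direction of each rate.
- Keep the total as description only.
- Exclude the referral assessment visit that defines group 1 from the counted contacts, or flag it and report the rates with and without it.
- Use the same contact categories in the outcome section and in Statistical considerations, so that the parts add up to the total.

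The models and register data are already planned, so this is mainly a reordering, plus a rule for one visit. The cost is fewer events and a somewhat wider interval for the leading result. The comparison of assessed with declining patients remains observational and should be described as such.

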### Study design

This is a prospective longitudinal study with 5 years follow-up from the date of inclusion.

The power calculation is based on the assumption that the prevalence of COPD will be twice the prevalence in the Danish background population (4.3%). With a power of 80% and a significance level of 0.05, a sample comprising 511 patients is required.

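### For patients assessed at the hospital clinic, the visit that places them in group 1 can also be counted as an outcome contact; group 3 lacks it by construction and nothing excludes it

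*Protocol article*

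**What the plan says.** - **Clock.** Study design: "This is a prospective longitudinal study with 5 years follow-up from the date of inclusion".
- **Groups.** Five-year follow-up outcome measures defines "1) the group with no previous COPD diagnosis, impaired lung function at screening, and who underwent further assessment" and "3) the group with no previous COPD diagnosis, impaired lung function at screening, and who declined further assessment". Group 2 is patients with an earlier COPD diagnosis. No time limit is set on when the assessment has to happen.
- **Route.** Methods, in the text after Fig. 1, says that patients with impaired lung function "will be referred to the respiratory outpatient clinic at the hospital for further diagnostic work-up", whether or not they already have a lung condition. Where that is not feasible, they are told to see their general practitioner (GP).
- **Ascertainment.** Data collection, Baseline: local investigators look in hospital bookings and notes for attendance at respiratory medicine. Whether a J44 diagnosis was confirmed is a separate question.
- **Outcome.** Five-year follow-up outcome measures counts hospital contacts "within each year of the 5-year follow-up (both outpatient visits and hospitalizations) with a diagnosis related to COPD for three patient groups". Clinical variables bases utilisation on every hospital contact, outpatient visits included, with no COPD restriction.
- **Model.** Statistical considerations compares contact rates among the three groups by Poisson regression and adds: "Sub-analyses for the rate of acute contacts and outpatient contacts will be conducted using models constructed in the same way as for all contacts".
- **Process measure.** Outcome measures already reports, on its own, the proportion examined at a clinic or by a GP within 4 months of screening.

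**The concern.** Group membership depends on an event after inclusion. For clinic-assessed patients that event is a hospital outpatient visit inside the counting window, of a type that the outcome includes. The same visit can therefore act as exposure and as outcome. Group 3 is defined by its absence.

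The group 1 to group 3 rate ratio then exceeds 1 even if assessment changes nothing afterwards. The extra contact falls mainly in year 1, which the protocol reports separately. At stake is the comparison that serves the second objective, the five-year impact of screening and referral. Covariate adjustment cannot remove an event built into the group definition.

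**Working it through.** **The plan's own figure.** The only size calculation concerns prevalence: "With a power of 80% and a significance level of 0.05, a sample comprising 511 patients is required", for 4.3% against 8.6%. A two-sided two-proportion formula gives 512 per group (pooled variance) or 509 (unpooled), so 511 is reproduced. It has no bearing on the contact comparison, for which the article states no rate, group size or power.

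**Does the index visit qualify?**
1. Timing: it comes after inclusion, so it lies in the window.
2. Type: it is an outpatient visit, so it is included.
3. Diagnosis: under Clinical variables every clinic visit counts; under Five-year follow-up outcome measures it counts if given a COPD-related code.
4. Exclusion: the article has no landmark, delayed start or index-visit rule.

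**Formula.** Let λ be the contact rate per year, equal in both groups (no true effect), T the years of follow-up, and q the share of group 1 with one counted index visit. Expected contacts per patient are λT + q in group 1 and λT in group 3, so

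ratio = (λT + q)/(λT).

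λ and q are not in the article. They are assumed here and varied.

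**Over 5 years, q = 1**
- λ = 0.3: (1.5 + 1)/1.5 = 1.67
- λ = 0.5: (2.5 + 1)/2.5 = 1.40
- λ = 1.0: (5 + 1)/5 = 1.20
- λ = 2.0: (10 + 1)/10 = 1.10

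**Over 5 years, q = 0.5**
- λ = 0.5: (2.5 + 0.5)/2.5 = 1.20
- λ = 2.0: (10 + 0.5)/10 = 1.05

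**Year 1 alone, λ = 0.5**
- q = 1: (0.5 + 1)/0.5 = 3.0
- q = 0.5: (0.5 + 0.5)/0.5 = 2.0

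**Shorter follow-up.** With T = 3, λ = 0.5 and q = 1: (1.5 + 1)/1.5 = 1.67.

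**False-positive rate.** A two-group Poisson Wald test was simulated (20,000 runs, two-sided 5%, an assumed 50 patients per group, 5 years, λ = 0.5, no true effect). It rejects in 84% of runs with q = 1 and 32% with q = 0.5. With the index visit not counted (q = 0) the ratio is 1.00. The error rate is then 4.7% to 5.3% across the rates (0.2 to 2 per year) and group sizes (30 and 50) tried.

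**The case against.** A reader might infer that every assessed patient has at least one COPD-related contact by definition. The documents do not support that:
- The GP route is open, and a GP visit is not a hospital contact. Whether GP-assessed patients enter group 1 is unclear, because assessment is ascertained from hospital records.
- Under the COPD-restricted outcome, a work-up that ends without a COPD-related code is not counted. The article foresees this by stratifying on confirmed and non-confirmed diagnosis.

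So q may lie well below 1. This part of the objection stands.

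The plan also limits the damage. Yearly reporting confines a single early visit mainly to year 1, and the acute-contact sub-analysis is largely free of it. Group 2 is referred too, so the distortion is clearest for group 1 against group 3. All of this stands. But yearly reporting locates the excess without removing it, and the rate in Statistical considerations uses the whole follow-up.

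It can be argued that referral visits belong to the effect of a screening-and-referral strategy, so that counting them is a choice of estimand. That does not rescue this contrast. Groups 1 and 3 were both screened and both referred; the visit is what separates them. For the same reason, a ratio above 1 could not be read as screening raising hospital use.

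Finally, a condensed article may leave counting rules to an analysis plan. Here, though, the start of follow-up, the groups and the outcome content are all stated, and following them as written produces the overlap.

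**Conclusion.** The concern holds in limited form. For clinic-assessed patients in group 1 the index visit is eligible to be counted, group 3 cannot have it, and no rule removes it. The ratio under no effect exceeds 1 whenever q is above 0.

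If q = 1, the five-year ratio runs from 1.67 down to 1.10 for rates of 0.3 to 2.0 per year. At 0.5 per year, halving q lowers it from 1.40 to 1.20. These sizes rest on assumed rates, an assumed q and one counted visit per patient; more work-up visits would raise them. The false-positive figures also rest on an assumed group size.

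The all-contact model, the outpatient sub-analysis and the year 1 results are affected. The prevalence objective and its sample size are not.

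**What to change.** Add a landmark rule to the five-year contact outcome. Assign groups by assessment status at 4 months after screening, the window that Outcome measures already uses, and start both the contact count and the follow-up time there in all groups. Fixing membership at the same point matters because the group definitions set no time limit on assessment. The first yearly interval then needs restating, since only 8 of its 12 months remain.

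Alternatively, exclude the index screening-referral visit from the counts whenever it occurs. This keeps early follow-up but leaves membership dependent on a later event, and further visits of the same work-up would still count.

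Under either rule, report the referral visits separately through the existing 4-month process measure, and state whether GP-assessed patients belong to group 1.

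The landmark costs the contacts and deaths of the first 4 months, which leave the group comparison, and work-up visits after month 4 stay in the count. It needs no new data collection: the linked registers and the hospital bookings are already planned sources.

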### Outcome measures

From the baseline examination, the study will report the following outcome measures:Prevalence of non-reversible airflow limitation that is a post-bronchodilator FEV1/FVC ration< 0.70Proportion of diagnosed vs. undiagnosed COPD at the time of screening (with a previous diagnosis of COPD defined as a patient-reported diagnosis in the baseline questionnaire)Proportion of patients diagnosed with lung function impairment (FEV1/FVC ratio < 0.7) subsequently examined at a respiratory outpatient clinic/GP within 4 months from screening.Prevalence of patients diagnosed with COPD after screening (identified by ICD10 code J44, or redeemed prescriptions of COPD treatment)Prevalence of participating current smokers who wish to stop smoking (patient-reported outcome in the baseline questionnaire)Prevalence of patients with identified lung function impairment (FEV1/FVC ratio < 0.7) at screening, who have a desire to quit smoking (patient-reported outcome in the baseline questionnaire)Prevalence of patients who want to quit smoking (patient-reported outcome in the baseline questionnaire) and accept the smoking cessation support offers (identified by social nurse notes in patient report).

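### The clinic visit that places a patient in the assessed group can be counted as an event in the COPD contact rate, so the assessed-versus-declined ratio exceeds 1 with no true effect

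*Protocol article*

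**What the plan says.** All references are to the protocol article.

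- **Clock.** Study design: "This is a prospective longitudinal study with 5 years follow-up from the date of inclusion".
- **Outcome.** Five-year follow-up outcome measures lists first the hospital contacts per person-year in each of the five years, "both outpatient visits and hospitalizations) with a diagnosis related to COPD for three patient groups".
- **Groups.** The same section defines group 1 as "1) the group with no previous COPD diagnosis, impaired lung function at screening, and who underwent further assessment" and group 3 as "3) the group with no previous COPD diagnosis, impaired lung function at screening, and who declined further assessment". Group 2 has a previous diagnosis.
- **Where assessment happens.** According to the text after Fig. 1 in Methods, patients with impaired lung function "will be referred to the respiratory outpatient clinic at the hospital for further diagnostic work-up". The general practitioner is the fallback.
- **How attendance is established.** Data collection (Baseline) has local investigators look it up in outpatient bookings and physician notes once recruitment is full.
- **Analysis.** Statistical considerations divides contacts by follow-up length and compares the three groups by Poisson regression with confounders. There the non-assessed group reads "undiagnosed COPD without further assessment, and previously diagnosed COPD at inclusion, using a Poisson regression model". Separate models are planned for acute and for outpatient contacts.
- **A different contact definition.** Clinical variables says use of services is "evaluated based on all hospital contacts, including outpatient visits, admissions, and emergency department (ED) visits", with no restriction to COPD.

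The article nowhere excludes the work-up visit, sets a landmark or treats assessment as time-varying.

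**The concern.** Group 1 is defined by something that happens after the clock starts, and that something is usually a hospital outpatient visit, which is one of the event types counted. The visit therefore works twice: it sorts the patient into group 1 and, if it carries a COPD-related diagnosis, adds to group 1's numerator. A patient in group 3 cannot have that event. Covariates in a Poisson model cannot remove an event that is part of the group definition.

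The article's second objective is the five-year impact of opportunistic screening and referral, and this comparison is its first-listed answer. Followed as written, it would tend to report that assessed patients use hospital services more, even if assessment changed nothing afterwards. Because rates are reported for each year, the most distorted figure, year 1, would be published on its own.

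Two inconsistencies add to this. Group 3 is patients who turned assessment down in one section and patients who simply had none in another. The contact outcome is COPD-related in one section and all hospital contacts in another. Each choice changes what is counted or who is compared.

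**Working it through.** **Plan's own figure.** None bears on this point. The only design figure, 511 patients, belongs to the prevalence comparison.

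**Inputs from the article.** Follow-up of 5 years from inclusion; outpatient visits counted; group 1 set by later assessment; person-time ending at death or dropout.

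**Assumed inputs, because the article gives none.** Contact rate r = 0.3 or 1.0 per year, identical in both groups (no true effect); constant mortality m = 8% per year; 60% uptake; assessment at a uniformly distributed time between 0.05 year and 4 months; k counted work-up visits per assessed patient.

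**Step 1: person-time.** Expected person-years over H years are (1 − e^(−mH))/m.

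- H = 5: (1 − e^(−0.40))/0.08 = 4.12
- H = 1: (1 − e^(−0.08))/0.08 = 0.961

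**Step 2: null rate ratio, group 1 versus group 3.** Ratio = 1 + k/(r × person-years).

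| k | r per year | 5-year ratio | Year-1 ratio |
|---|---|---|---|
| 1 | 0.3 | 1 + 1/(0.3 × 4.12) = 1.81 | 1 + 1/(0.3 × 0.961) = 4.47 |
| 1 | 1.0 | 1 + 1/4.12 = 1.24 | 1 + 1/0.961 = 2.04 |
| 0.5 | 0.3 | 1 + 0.5/(0.3 × 4.12) = 1.40 | 2.73 |
| 0.5 | 1.0 | 1 + 0.5/4.12 = 1.12 | 1.52 |
| 2 | 0.3 | 1 + 2/(0.3 × 4.12) = 2.62 | 7.94 |

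A simulation in which group 1 patients must survive to their assessment, and so have slightly more person-time, gives about 1.8 and 1.24 over five years and 4.4 and 2.0 in year 1 for k = 1. Over a wider grid (r from 0.1 to 1.0, mortality 5% to 15% per year, 50% uptake, k = 1) the five-year null ratio runs from about 1.2 to 3.8. It is above 1 throughout.

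**Step 3: immortal time and the contact rate.** With the work-up visit left out but the clock still at inclusion, the simulated null contact ratio is 0.997 to 1.003. Immortal time barely moves this outcome when the contact rate is constant.

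**Step 4: immortal time and mortality, if groups were compared on it.** If patients who die before assessment join the unassessed group, the null five-year mortality ratio is about 0.89 at 60% uptake and about 0.81 at 80%. If group 3 holds only true decliners, a smaller distortion remains. The mean wait to assessment is (0.05 + 0.333)/2 = 0.19 year. Group 1 person-time is 0.19 + (1 − e^(−0.08 × 4.81))/0.08 = 4.18 years. The ratio is 1 − 0.19/4.18 = 0.95.

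**Step 5: after a 4-month landmark.** Classifying at 4 months and counting only later contacts, deaths and person-time among those alive gives null contact ratios of 0.998 to 1.003 and mortality ratios of 0.995 to 1.004 across the same grid.

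**The case against.** Several points on the other side are sound.

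- **Not every group 1 patient has a counted visit.** A reader might infer that each starts with at least one event by definition. The article does not support that. The outcome counts only contacts with a COPD-related diagnosis, a work-up that does not confirm COPD need not carry one, and assessment by a general practitioner is not a hospital contact. The half-counted rows above allow for this. The claim would hold for every clinic-assessed patient only under the all-contacts wording in Clinical variables.
- **Mortality.** A reader might infer that the plan will show a spurious survival benefit. Better survival is anticipated in the Abstract and deaths are collected, but neither the follow-up outcomes nor Statistical considerations specifies a between-group mortality comparison. The ratios of about 0.8 to 0.9 also need early deaths to fall in the unassessed group, which the statistics wording implies and the outcome wording does not.
- **The 4-month window.** "subsequently examined at a respiratory outpatient clinic/GP within 4 months from screening" describes a baseline proportion. It does not define group membership, for which no window is stated.
- **Existing protection.** Yearly reporting leaves years 2 to 5 largely free of the initial work-up, and the acute-contact model largely avoids it. The outpatient model, however, concentrates it.
- **The wording on all contacts in Statistical considerations** may mean all contact types rather than all diagnoses. Only Clinical variables is plainly broader.
- **Referral is part of what is studied**, so added clinic use is arguably an effect. That would justify describing work-up visits. It does not justify counting them in a contrast between groups that those same visits define.

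These limit the size and reach of the point. They do not remove the double use of the visit in the first-listed outcome.

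**Conclusion.** The point stands for the contact rate. As written, the group 1 versus group 3 ratio exceeds 1 with no true effect whenever some assessed patients have a COPD-coded clinic work-up. The direction follows from the text. The size depends on the assumed contact rate, mortality and share of assessed patients with a counted visit: about 1.12 to 1.8 over five years for half to one visit per patient at 0.3 to 1.0 contacts per year, and more in year 1 and in the outpatient sub-analysis.

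Immortal time is a secondary matter. It leaves the contact ratio at about 1.00 and would matter only for a mortality comparison the article does not set out. The prevalence objective is untouched. The article names no primary follow-up outcome, so the affected outcome is first-listed rather than primary. Because clock, groups and outcome are all fixed in the article, this is not a detail left to an analysis plan.

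**What to change.** 1. Define the groups by assessment status at a landmark after inclusion. Four months is a natural choice, borrowed from the baseline proportion in Outcome measures; state that it now also defines the groups.
2. For all three groups, count contacts and person-time only after the landmark, among those alive then, and leave out any later contacts that still belong to the initial work-up. Work-up visits can be reported descriptively.
3. Apply the same landmark to any between-group mortality comparison.
4. Use one definition of group 3 (declined, or not assessed for any reason) and one definition of the contact outcome (COPD-related, or all hospital contacts) in Five-year follow-up outcome measures, Clinical variables and Statistical considerations.
5. Give prominence to the acute-contact analysis already planned. The stated COPD-related outcome need not be replaced: all-cause acute contacts would answer a different, less specific question.

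**Cost.** Wording and programming on register data. With a 4-month landmark, 4 of 60 months and the early deaths leave the comparison. Self-selection into assessment is not cured, so the report should say that the contrast is not the causal impact of screening.
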